## Abstract

**Background:**

Influenza can fall into three categories according to severity: mild influenza, severe influenza, and critical influenza. Severe influenza can result in critical illness and sometimes death particularly in patients with comorbidities, advanced age, or pregnancy. Neuraminidase inhibitors (NAIs) are the only antiviral drugs in widespread use for influenza. However, the effectiveness of NAIs against severe influenza is uncertain. New effective drugs or regimens are therefore urgently needed. *Qiangzhu-qinggan (QZQG)* formula has been found to be effective against influenza virus infection during long-term application in China, which lacks support of evidence-based clinical trial till now. This study is designed to assess the efficacy and safety of *QZQG* formula as an adjuvant therapy in adult patients with severe influenza.

**Methods:**

This protocol is drawn up in accordance with the SPIRIT guidelines and CONSORT Extension for Chinese herbal medicine formulas. This is a randomized, placebo-controlled, double-blind, multicenter trial. Two hundred twenty-eight adults with severe influenza are randomly assigned in a 1:1 ratio to *QZQG* or placebo for 7 days. All participants need to receive 1 day of screening before randomization, 7 days of intervention, and 21 days of observation after randomization. The primary outcome is the proportion of clinical improvement, defined as the proportion of patients who met the criteria of 3 points or less in the seven-category ordinal scale or 2 points or less in National Early Warning Score 2 within 7 days after randomization.

**Discussion:**

This is the first randomized, controlled, parallel, double-blind clinical trial to evaluate the efficacy and safety of traditional Chinese herbal formula granules as an adjuvant therapy in adult patients with severe influenza. This study aims to redefine the value of traditional Chinese herbal medicines in the treatment of virus-related respiratory infectious diseases and serves as an example of evidence-based clinical trials of other Chinese herbal medicines.

**Supplementary Information:**

The online version contains supplementary material available at 10.1186/s13063-021-05929-8.

## Introduction

### Background and rationale {6a}

“Spanish flu” pandemic in 1918 was described as the most devastating viral pandemic in history caused by an H1N1 influenza A virus that infected over 500 million and killed between 50 and 100 million people [1]. Influenza infection remains serious today. The Centers for Disease Control and Prevention (CDC) estimated that influenza virus infection caused more than 35.5 million illnesses, more than 16.5 million medical visits, 490,600 hospitalizations, and 34,200 deaths during the 2018–2019 influenza season in the USA [2]. It is estimated that an annual mean of 88,100 (95% CI 84,200–92,000) influenza-associated excess respiratory deaths occurred in China during the 2010–2011 through 2014–2015 seasons, corresponding to 8.2% (95% CI 7.9–8.6) of all reported respiratory deaths [3]. Seasonal influenza worldwide is estimated to cause 291,243–645,832 influenza-associated respiratory deaths annually [4]. Although mostly a self-limited disease, 5–10% of hospitalized patients with influenza required ICU admission mainly because of acute respiratory failure [5]. Influenza can be divided into three categories according to severity: mild influenza, severe influenza, and critical influenza [6]. Severe influenza is one of the main causes of critical illness and death particularly in patients with co-morbidities, advanced age, or pregnancy [4].

Antiviral drugs currently approved for use in China, the USA, and the European Union include the neuraminidase inhibitors (NAI) and adamantane derivatives [6–8]. Currently circulating seasonal influenza viruses are resistant to the adamantane derivatives and so the use of these agents is not recommended [7, 8]. It is advised that clinicians should start antiviral treatment in severe influenza as soon as possible with a single neuraminidase inhibitor (either oral oseltamivir, inhaled zanamivir, or intravenous peramivir) [9]. Baloxavir marboxil (XofluzaTM; baloxavir), a novel, cap-dependent endonuclease inhibitor, received its first global approval in Japan on 2018 for the treatment of influenza A or B virus infections in pediatric and adult patients [10]. However, adequate evidence-based clinical trials have not been conducted to define which antiviral drug severe influenza can benefit from [11]. As recommended by the WHO’s Global Influenza Strategy for 2019–2030, it is urgent to develop better treatment regimen for influenza [12].

A large amount of clinical evidence confirmed the efficacy and safety of Traditional Chinese medicine (TCM) in viral respiratory infections. As a major adjuvant therapy, TCM has been widely used to prevent and treat virus-related respiratory infection and included in the recommended treatment regimens for influenza in China [6]. A prospective, nonblinded, randomized controlled trial (RCT) in 2011 found that time to fever resolution was reduced by 19% (CI, 0.3% to 34%; *P* = 0.05) with oseltamivir plus *maxingshigan–yinqiaosan* compared with oseltamivir [13]. A RCT including 244 patients with influenza A virus infection in China has shown that *Lianhuaqingwen* capsule significantly reduced the severity of illness and the duration of symptoms including fever, cough, sore throat, and fatigue (*P* < 0.05) [14]. In a meta-analysis of 31 RCTs including 5514 cases of influenza [15], the authors concluded that TCM had significantly increased clinical efficacy compared with placebo or no intervention (93.46% vs. 79.03%, respectively; odds ratio, 3.99 [95% CI, 3.32 to 4.78]; *P* < 0.001), and no serious adverse effects were reported.

The mechanisms of TCM in treating influenza may include both antiviral and immunomodulatory effect. Numerous herbal extracts were shown to have antiviral effects against the influenza virus with multiple herbal antiviral targets mainly including hemagglutinin, neuraminidase, and matrix 2 proteins, which possess the ability to inhibit resistant influenza strains and have great application potential and scientific value for addressing the problem of emerging influenza antiviral resistance [16]. Many herbs exhibit beneficial immunomodulatory effects for the rapid recovery of viral infections [17, 18]. It is reported that *Jiawei-Yupingfeng-Tang* can alleviate influenza-induced lung lesions with both antiviral and immunomodulatory activity [19]. *Lianhuaqingwen* capsule was shown to exert broad-spectrum effects on a series of influenza viruses, including the newly emerged H7N9, and particularly regulates the immune response of virus infection [20].

*QZQG* formula is the combination and innovation of two ancient TCM formulas including *Jiuweiqianghuo* Decoction and *Zhuyeshigao* Decoction, which have been used in treating exogenous febrile disease (acute upper or lower respiratory tract infection) for hundreds of years. Our preliminary data show that the *QZQG* formula may improve influenza-like symptoms, shorten the course of disease, and reduce the proportion of critical illness (data not shown). However, no data are available from large-scale randomized controlled trials on the efficacy of *QZQG* and its adverse effects. Therefore, we aim to perform the first double-blinded, randomized, placebo-controlled trial to make clear the efficacy and safety of *QZQG* in adults with severe influenza. In the global context of COVID-19 pandemic, this trial will help to understand the value of traditional Chinese medicine as adjuvant therapy in severe and critically ill patients with respiratory viral infectious diseases such as influenza and COVID-19.

## Objectives {7}

Empirical evidence based on long-term clinical application shows that *QZQG* formula can effectively resist influenza virus infection. However, there are currently no reliable data from evidence-based clinical trials. We aim to carry out this trial to evaluate the efficacy and safety of QZQG formula plus western medicine regimen compared with placebo plus western medicine regimen in adults with severe influenza.

## Trial design {8}

This study was designed as a multicenter, randomized, parallel, double-blind, placebo-controlled trial. Eligible participants will be randomly divided into two groups at a 1:1 ratio: *QZQG* group and placebo group. Randomly assigned numbers will be provided by a third-party research institution (School of Public Health, Fudan University, China). All enrolled patients will receive 1 day of screening, 7 days of intervention, and 21 days of observation.

## Methods: participants, interventions, and outcomes

### Study setting {9}

This trial will be conducted in Longhua Hospital Affiliated to Shanghai University of Traditional Chinese Medicine, Huashan Hospital Affiliated to Fudan University, The First Affiliated Hospital of Anhui University of Traditional Chinese Medicine, Hefei Infectious Disease Hospital, Jiangsu Provincial Hospital of Traditional Chinese Medicine, Jiangsu Provincial Hospital for Infectious Diseases, and Zhejiang Provincial Hospital of Traditional Chinese Medicine. Prior to the trial, all personnel are trained in Longhua Hospital to ensure that the physicians and staff participating in the trial at every center fully understand all aspects of the trial (Fig. 1).

**Fig. 1 Fig1:**
[figure not shown]
Study flowchart. Participants with severe influenza will be recruited, and they will be assigned randomly into two different groups. All participants will accept the 1-day screening, 7-day intervention, and 21-day observation. The data were collected to determine the efficacy and safety of *QZQG* Formula as an adjuvant therapy

### Eligibility criteria {10}

Male and female patients with severe influenza aged 18–65 years are eligible for study participations. The diagnostic criteria for severe influenza referred to the “Scheme for diagnosis and treatment of influenza” issued by the National Health Commission of China in 2020 [6]. Patients will be enrolled if they conform to all inclusion criteria. However, they will not be enrolled if they have one of the exclusion criteria, rejection criteria, or termination standards.

#### Inclusion criteria

*The inclusion criteria are as follows:*
Diagnosis of influenza A and/or B by a positive Rapid Influenza Diagnostic Test (RIDT) or reverse transcriptase-polymerase chain reaction (RT-PCR).• Positive results from local tests are acceptable if conducted within the 24 h prior to screening.• A patient with a negative RIDT may be enrolled if influenza is suspected based on local surveillance data or if the patient reports contact with a known case of influenza within the prior 7 days and all other inclusion criteria are met.Granting of written informed consent.Male or female aged 18 to 65 years at the time of signing informed consent form.Ability to comply with the study protocol, in the investigator’s judgment.Participants who require hospitalization for severe influenza or acquire influenza during hospitalization, the severity of which requires an extension of hospitalization.Participants will require at least one of the following objective criteria of severe influenza: (i) duration with axillary temperature over 39 °C ≥ 3 days, accompanied by severe cough, sputum, blood sputum, or chest pain; (ii) rapid respiratory rate (≥30 times per minute), difficulty breathing and cyanosis of lips; (iii) arterial oxygen saturation (SaO2)/ pulse oxygen saturation (SPO2) ≤94% in room air condition; (iv) requires ventilation or supplemental oxygen to support respiration; (v) with only one complication related to influenza (e.g., pneumonia, central nervous system involvement, myositis, rhabdomyolysis, acute exacerbation of chronic kidney disease, asthma or chronic obstructive pulmonary disease (COPD), severe dehydration, myocarditis, pericarditis, exacerbation of ischemic heart disease).The time interval between the onset of symptoms and randomization is within 96 h. The onset of symptoms is defined as either time of the first increase in body temperature (≥ 38 °C) or time when the patient experiences at least one general or respiratory symptom.Conforming to the standard of TCM syndrome differentiation.

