### Sample size {14}

Sample size calculations are based on the primary endpoint (the proportion of clinical improvement within 7 days after randomization). At the 5% significance level, a total of 101 patients per group is required to achieve 90% power and to determine an increase of 20% in the proportion of clinical improvement between *QZQG* group and the placebo group, assuming that the clinical improvement rate within 7 days after randomization of the placebo group receiving oseltamivir plus routine symptomatic treatment is about 50%. With an estimated dropout rate of 10–20%, a total of 228 patients are planned to be enrolled. If the initial hypothesis is not rejected, subsequent comparison is considered exploratory, and no conclusion is made.

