### Definition of analysis population relating to protocol nonadherence {20c}

The intent-to-treat (ITT) population is defined as all randomized patients, whether or not the patient received the assigned treatment. The ITT patients will be analyzed according to the treatment assigned at randomization. The ITT population includes the patients who agree to enroll in the study and sign an informed consent form. However, ITT population involves those who have never received study drugs or never completed observation records. Efficacy analyses will be conducted for the modified intent-to-treat (mITT) population. This is defined as all patients randomized who received at least one dose of *QZQG* formula and were centrally assessed as RT-PCR positive for influenza at any timepoint, with patients grouped according to the treatment assigned at randomization. The per-protocol set is used to analyze the main outcome for evaluating efficacy and to examine the consistency of the results from the mITT. The PPS is defined as follows: (1) full compliance with inclusion and exclusion criteria; (2) the compliance of medication consumption is over 80%; (3) the patients complete the test and record of the outcome and safety evaluation at every time node; and (4) completion of the clinical trial without major protocol violation. The safety analysis set (SAS) is defined as patients who received any amount of study treatment. Patients will be analyzed according to the treatment received. Patients who were randomized to the study but who did not receive any study drug will not be included in the safety population. The SAS will be used for the analysis of all safety indicators. Multiple imputation will be used for missing data.

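### The per-protocol set does not require a positive central RT-PCR, so it can hold patients whom the mITT it is meant to check leaves out

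*Protocol article*

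**What the plan says.** Three sections of the protocol article bear on this.

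- **Inclusion criteria.** The first criterion asks for "Diagnosis of influenza A and/or B by a positive Rapid Influenza Diagnostic Test (RIDT) or reverse transcriptase-polymerase chain reaction (RT-PCR"). A sub-item then makes an exception: "A patient with a negative RIDT may be enrolled if influenza is suspected based on local surveillance data". A second route under the same exception is exposure to a confirmed case in the preceding week, as told by the patient; the remaining criteria still apply. No RT-PCR result is asked for before such a patient is randomized.
- **Definition of analysis population (20c).** "Efficacy analyses will be conducted for the modified intent-to-treat (mITT) population". Besides a dose condition, membership requires that patients were "centrally assessed as RT-PCR positive for influenza at any timepoint, with patients grouped according to the treatment assigned at randomization". The per-protocol set is given two tasks: analysing the main outcome, and checking that the result agrees with the mITT. It has four conditions: "1) full compliance with inclusion and exclusion criteria"; medication compliance above 80%; complete outcome and safety assessments; and no major violation. None mentions RT-PCR or mITT membership. Multiple imputation is named for missing data.
- **Sample size (14).** The requirement is 101 per group for 50% versus 70%. "With an estimated dropout rate of 10–20%, a total of 228 patients are planned to be enrolled". No other loss is named.

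**The concern.** A per-protocol analysis is useful as a check on the mITT when the two sets differ in adherence and completeness alone. Here they can also differ in whether the patient had confirmed influenza. A patient admitted through the exception has complied with the inclusion criteria, so a negative central RT-PCR does not breach the first per-protocol condition. The same result removes that patient from the mITT. If the two analyses disagree, the reader cannot tell whether adherence or diagnosis is the reason. If they agree, the agreement is harder to interpret for the same reason.

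A second, smaller matter follows from the mITT rule. Every patient who is never centrally RT-PCR positive takes one of the 228 places and adds nothing to the efficacy population, and the sample-size section does not say what share is expected.

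**Working it through.** **Step 1: follow one patient through the definitions.** Take a patient with a negative RIDT, enrolled on surveillance data or contact, who takes all study drug, completes every assessment and is never centrally RT-PCR positive.

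| Rule | Met? |
|---|---|
| Inclusion criterion 1 (through the exception) | yes |
| Per-protocol 1: eligibility | yes |
| Per-protocol 2: compliance above 80% | yes |
| Per-protocol 3: assessments complete | yes |
| Per-protocol 4: no major violation | yes; entry was permitted |
| mITT: central RT-PCR positive at any timepoint | no |

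The patient is in the per-protocol set and not in the mITT, so the first is not nested in the second. This step needs no assumed rate. A patient with a positive RIDT but a negative central RT-PCR reaches the same place.

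**Step 2: reproduce the plan's figure.** Inputs from the sample-size section: 50% versus 70%, 5% level, 90% power. The pooled-variance formula is

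n = [z_α √(2·0.6·0.4) + z_β √(0.5·0.5 + 0.7·0.3)]² / 0.2²

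- One-sided 5%: (1.645·0.693 + 1.282·0.678)² / 0.04 gives 101 per arm, the stated figure.
- Two-sided 5%: (1.960·0.693 + 1.282·0.678)² / 0.04 gives 124 per arm.

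The stated 101 is thus reproduced as a one-sided calculation, while the statistical methods section fixes two-sided tests. At 101 per arm, two-sided power is about 83%. That is a separate issue, and it explains why the baseline in Step 4 is not 90%.

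**Step 3: mITT headcount.** The mITT rule does not remove dropouts, so the headcount is 228·(1−x), where x is the assumed central RT-PCR-negative share. This takes every randomized patient in both arms to have had at least one dose of assigned treatment.

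**Step 4: patients with observed outcomes, and power.** With dropout at the low end of the stated range, the number observed is 228·0.9·(1−x). Half of that is n per arm, and two-sided power is

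Φ[(0.2√n − 1.960·0.693) / 0.678]

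| Assumed x | mITT headcount | Observed at 10% dropout | n per arm | Two-sided power |
|---|---|---|---|---|
| 0% | 228 | 205 | 102.6 | 83.8% |
| 5% | 217 | 195 | 97.5 | 81.8% |
| 10% | 205 | 185 | 92.3 | 79.7% |
| 15% | 194 | 174 | 87.2 | 77.4% |
| 20% | 182 | 164 | 82.1 | 74.8% |

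The plan's requirement is 2·101 = 202. On headcount, the mITT stays above 202 up to x = 1 − 202/228 = 11.4%. On observed outcomes at 10% dropout, the margin is 205 − 202 = 3 patients, which is used up once x passes about 1.6% (1 − 202/205.2).

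**The case against.** The strongest reply is that the design is coherent. Suspected cases are enrolled and efficacy is then assessed in a centrally confirmed mITT, so unconfirmed patients do not dilute that result. The per-protocol set is only a consistency check, and an analysis plan or the blind review of the data may refine it. The first part stands: the mITT result is protected. The second does not remove the point, because the article itself fixes both definitions and, as written, they do not nest.

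Several stronger readings are tempting, and the document does not support them.

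- **That the inclusion criterion contradicts itself.** It states a rule and then an express exception that still requires all the other criteria to be met. Those include hospitalization, an objective severity criterion, onset within 96 h and the TCM pattern.
- **That RIDT-negative patients are dropped from the mITT.** Only patients never centrally RT-PCR positive are dropped. A false-negative RIDT with a positive central result stays in, and a RIDT-positive patient without one goes out.
- **That the mITT itself shrinks to 195, 185, 174 or 164.** Those are counts with observed outcomes. Dropout is not an mITT exclusion, and missing data are to be imputed.
- **That RT-PCR-negative entry explains the whole shortfall from 90% power.** The step from 90% to about 84% is present at x = 0.
- **That the RIDT-negative entry route must be closed.** Whether to keep it is a design choice. Requiring a local RT-PCR would presume results within the one-day screening at every centre, which the article does not state. It also would not guarantee nesting, since mITT status rests on the central test.

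**Conclusion.** The point holds for the population definitions. A patient never centrally RT-PCR positive can be analysed per protocol and be absent from the mITT, which weakens the per-protocol analysis in the role the article gives it. This follows from the text alone. How far the two results could diverge cannot be derived, because neither the number of such patients nor their outcomes are given.

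The sample-size part is a matter of disclosure. Over an assumed 5% to 20% RT-PCR-negative share with 10% dropout, two-sided power falls by about 2 to 9 percentage points from a base of about 84%. These figures rest on the assumed share, equal loss in both arms, the planned 50% and 70%, and analysis of observed outcomes only. The document does not show that the mITT will fall short of 202. By headcount it would do so only if the share passed about 11%.

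**What to change.** 1. In the analysis-population section (20c), define the per-protocol set as patients in the mITT, hence centrally RT-PCR positive at any timepoint, who also meet conditions (1) to (4). The word central matters, because a positive local RT-PCR would not ensure mITT membership. The cost is one sentence and a slightly smaller per-protocol set.
2. In the sample-size section (14), state that the 228 allows for dropout only, and give the expected central RT-PCR-negative share with its source and the resulting two-sided power. The cost is a short addition. If the resulting power is judged too low, the sponsor would then have to decide whether to enrol more patients.

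Neither change requires altering the entry criteria.

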#### Exclusion criteria

*The exclusion criteria are as follows:*
Participants hospitalized for exclusively social reasons (e.g., lack of caregivers at home).Participants expected to be discharged within 48 h, according to the investigator’s judgment.Participants weighing < 40 kg.Participants who have received more than 48 h of antiviral treatment for the current influenza infection prior to screening.Participants with known severe renal impairment or receiving continuous renal replacement therapy, hemodialysis, peritoneal dialysis.Participants with any of the following laboratory abnormalities detected within 24 h prior to or during screening (according to local laboratory reference ranges:• Alanine transaminase (ALT) or aspartate transaminase (AST) level > 5 times the upper limit of normal (ULN).• ALT or AST > 3 times the ULN and total bilirubin level > 2 times the ULN.Any serious medical condition or abnormality in clinical laboratory tests that, in the investigator’s judgment, precludes the participant’s safe participation in and completion of the study.With mental changes or convulsions (e.g., slow response, drowsiness and restlessness).With severe gastrointestinal symptoms (e.g., severe nausea, vomiting, diarrhea and even dehydration).With one of the following critical illnesses: respiratory failure, acute necrotic encephalopathy, septic shock, multiple organ dysfunction, or other serious clinical conditions requiring intensive care.With tuberculosis, measles, AIDS, or other infectious diseases.Women who are pregnant (including a positive pregnancy test at enrollment), breastfeeding, or within 2 weeks post-partum.Known history of allergy or severe intolerance of oseltamivir and herbal medicines, as determined by the investigator.Currently or have been involved in another anti-influenza treatment trial in the last 28 days.Patients who have been treated with oral Chinese medicine within 4 weeks.Patients who, in the opinion of the investigator, would be unlikely to comply with required study visits, self-assessments, and interventions.

